**6.2 Dietary Intervention with selenium-enriched onions**

Selenium-enriched and un-enriched onions (groups 5 and 6) will only be studied during years 2 and 3 (the onions will be grown in year 1 and 2 of the project). The possible side effects to eating any onions are bloating and wind. This will be clearly stated in the volunteer information sheet (annex 4).

Selenium-enriched onions (in the form of 3 to a maximum of 5 meals per week), providing the equivalent of 50μg selenium/day.

Un-enriched onions (in the form of 3 to a maximum of 5 meals per week), providing <1μg selenium per day.

On Day 1 of the study, the volunteer will be asked to attend the unit in the morning between the hours of 7:30 and 9:00am to give their first blood and saliva sample all subsequent procedures will be the same as those outline in section 6.1. The only difference will be that after the consumption of a standard unit breakfast (a range of cereals, toasted bread, tea and coffee), the volunteer will be supplied with up to one months supply of their onion test meals in a container that will ensure that the meals remain frozen (cool box or cool bag). This will be assessed on an individual basis as the volunteer may not be able to transfer the food in a suitably frozen state to their freezer at home, or may not in fact be going directly home after their visit to the HNU resulting in the thawing of the meal. If this is the case, a food delivery will be arranged (by refrigerated van, hired for this purpose) prior to their commencement of the study (Prior to day 1). The volunteer will also be given a container for carrying out a 24hour urine collection prior to their next visit in week six. The volunteer will not know whether their test meals contain the selenium enriched onions or the un-enriched onions. This will have been randomly allocated on recruitment. The research scientist in charge of the study will also not know, but the allocation of the onions meals will be supervised by a scientist not on the study. The volunteer will be asked to eat up to 5 of the onion test meals each week for the next 12 weeks, returning to their normal diets in between onion meals.The volunteer will be given a record sheet to indicate at which time of each day they are consuming their onion meal (Annex 16).

Arrangements will be made with the volunteer for suitable times for the remainder of their meals to be delivered either by refrigerated van or by a member of the study team; alternatively volunteers will be offered the option to pick up the meals themselves from the Human Nutrition Unit at their own convenience. The volunteer will be advised to contact [name] ([name]) or [name] ([name]) if they have any problems or queries associated with the consumption of the onion test meals.

The same procedure will be followed in week six (day 42±2days) as outlined in section 6.1 for the supplementation intervention, the only exception being that the volunteer may well be given another batch of meals, or arrangement will have been made for the delivery of test meals.

The same procedure will be followed in week ten as outlined in section 6.1, the only exception being that after the administration of the flu vaccine, the volunteer will continue to consume their thrice weekly onion based test meals as per usual. The volunteer will return to the unit to give fasted blood samples 7 (week 11) and 14 (week 12) days post vaccination (80mL each time) and a saliva sample in week 12.

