# 4.0 Study Design

## 4.1 Overview

A 12 week intervention will be carried out in which 6 groups of 50-64y old men and women (n=24 per group) with low plasma (or serum) selenium are fed one of three doses of selenium (50, 100 or 200µg/d) as selenium enriched yeast (Se-yeast) tablet, a placebo tablet, selenium-enriched onions (equivalent to 50µg/day selenium) or un-enriched onions during the summer, autumn and winter periods (July-February). Subjects will be given an influenza viral challenge 10 weeks after starting the intervention. Volunteers will be informed that our study also vaccinates during the months December to February which is outside the traditional flu vaccination period adopted by the NHS. The precise time of vaccination for the volunteers will depend on their intervention starting date and may therefore take place in the period between December to February. Health care workers and those who are offered free flu vaccination from the NHS will not be eligible to take part in the study during the months of December to February.

The Se-yeast treatment will take place over 3 years; the onion treatment will take place during years 2 and 3 (the onions will be grown in years 1 and 2 for consumption the following year). The onions will be stored for a number of months and then incorporated into meals which will be stored at -18°C until required.

The control subjects will take a placebo and undergo the same tests. Venous blood samples will be taken pre-vaccination at baseline (week 0, 80mls), 6 (40mls) and 10 weeks (80mls) then post vaccination at 11 (80mls) and 12 weeks (80mls). Saliva samples will be obtained at baseline (pre-vaccination) and 12 weeks (post-vaccination). Blood samples will be used for the assessment of plasma selenium concentration (Q-ICPMS), plasma vitamin E (HPLC), selected selenoproteins, selenium-responsive genes, protein expression, and cellular and humoral immune response. The saliva samples will be tested for antibody titres to influenza antigens. A 24hour urine collection will be made during week 6 to determine selenium concentration.

Week 0

6

10

11

12

[figure not shown]

Up to 5 onion based test meals consumed

per week for 12 weeks

[figure not shown]

-Se

+Se

1 capsule taken every day for 12 weeks

Fasted Blood sample (60mL)

24hour urine collection

Influenza virus vaccination

Volunteer groups taking part in study

Saliva sample

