## 6.5 Supply of Food and Supplements to Volunteers

**6.51 Selenium-enriched onions**

The selenium-enriched and un-enriched onions will be grown by the Division of Plant Science, University of Nottingham, under the supervision of [name], who is an authority on mineral nutrition of crops and is currently supervising a BBSRC CASE studentship programme on selenium enhancement with Hydro-Agri UK. The UK’s most popular variety of main crop onion (*Allium cepa* L., cv. Renate; a Rijnsburger type) will be grown by an experienced team of specialist horticultural scientists using standard commercial UK horticultural practices, and with the expertise in selenium fertilisation gained from the BBSRC CASE studentship. The onion crops will be harvested in August 2005 and 2006, and stored to ensure quality material is delivered for the intervention study. The selenium content of onions is approximately 1μg/100g (i.e. 0.9μg/onion) whereas Se-enriched onions contain 70-90μg/100g (i.e. 60-80μg/onion). Sufficient onions (~3,000) will be grown to provide enough onions for up to five meals per week for each volunteer for the 12 week intervention (Se-enriched: up to 5(meals) x12(weeks) x24(subjects); un-enriched: 5(onions) x12(weeks) x24(subjects)).

We will request that the different onions are labelled with different coloured tags (for example, or put in different coloured sacks). Meals will then be prepared with say, the red labelled onions, or the blue labelled onions without any one in the kitchen or the leading scientist knowing whether the red or blue labels related to enriched or un-enriched onions. As well as asking the manufactures to keep records of the coding i.e. red for selenium-enriched and blue for un-enriched say, we would ask that we too had an envelope with the information. This information would be held by a scientist not associated with the project, with the information being disclosed at the end of the study.

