# 7.0 Statistical Analysis

Power calculations were done so that, out of the six study groups, a difference of 1 standard deviation in response variable between the minimum and maximum responding groups would be reliably detected. For example, for plasma selenium, previous studies (Shortt et al, 1997) suggest that the population standard deviation is 11.7, and so our sample sizes are designed to give an 80% chance of detecting a range of plasma selenium between the six groups of 11.7. For antibody secreting cells/500,000 lymphocytes and specific serum antibody (both at day 7 post-vaccination) the corresponding standard deviations are 76 and 19 respectively (Cox et al, 1999).

The power calculations also assumed that any effect of selenium supplementation would be proportional to the amount of supplementation, with enriched onions being equivalent to a supplementation of 50µg/day selenium and the un-enriched onions equivalent to no supplementation.

The power calculations were also based on the assumption that the data would be analysed using a one-way ANOVA model, the grouping having six levels (control, 50µg/day selenium, 100µg/day selenium, 200µg/day selenium, enriched onions, non-enriched onions). In order to be able to detect a range of 1 standard deviation between the groups with a power of 80%, a sample size of 144 (or 24 in each group) is sufficient. This allows for a drop-out rate of 25%, or in other words, finishing with 18 subjects in each group.

In the unlikely event of there being a year effect, and thus the two onion groups (but not the control and supplementation groups) being potentially compromised,24 subjects in each of the remaining 4 groups gives a power of 80% of detecting a range of 1 standard deviation in the response variable. This is based on using a two-way ANOVA model to analyse the data, with a three level year effect and a four level group effect (control, 50µg/d Se, 100µg/d Se, 200µg/d Se). It is important to stress however that we are aiming to recruit the full complement of 24 volunteers without the drop out rate of 25% as we feel there is a greater chance of compliance with the supplementation intervention.

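### The enriched-onion arm is credited with 50 µg selenium/day at any frequency from 3 to 5 meals a week, so its equivalence to the 50 µg/day Se-yeast group is not assured

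*Protocol*

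**What the plan says.** **Daily amount.** Section 4.1 lists "selenium-enriched onions (equivalent to 50µg/day selenium" among the six interventions. Section 6.2 ties the same amount to a range of meal frequencies: "Selenium-enriched onions (in the form of 3 to a maximum of 5 meals per week), providing the equivalent of" 50 µg selenium per day. The power calculation in section 7.0 goes on "with enriched onions being equivalent to a supplementation of" 50 µg/day, the amount in the Group 1 Se-yeast tablet (section 6.1).

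**Meals per week.** Section 6.2 gives 3 to 5 and then asks volunteers to eat as many as 5. Figure 1 (section 4.1) and section 6.51 also give 5 as an upper limit. For the period after vaccination, section 6.2 says that "the volunteer will continue to consume their thrice weekly onion based test meals as per usual".

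**Onion content and supply.** Section 6.51 states that "Se-enriched onions contain 70-90μg/100g (i.e. 60-80μg/onion" and that "Sufficient onions (~3,000) will be grown to provide enough onions for up to five meals per week for each volunteer for the 12 week intervention". Its breakdown is 5 × 12 weeks × 24 subjects in each onion arm. The 5 is labelled as meals for the enriched arm and as onions for the un-enriched arm.

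No section gives the number of onions per meal, or says that a meal's onion content depends on how many meals a volunteer eats.

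**The concern.** One daily amount is attached to a schedule that may vary by a factor of 1.67 between volunteers, or within a volunteer over time. The section on procedures after vaccination describes the lowest frequency as the usual one, whereas the crop is sized for the highest.

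This bears on the first objective in section 3.0, which is to examine two organic forms of selenium. Section 2.0 identifies them as SeMet in the tablets and, predominantly, SeMC in the onions. The enriched-onion arm is the only SeMC arm, and section 7.0 equates it with 50 µg/day, so the natural reading of any form comparison is onions against the 50 µg tablet. If the onion arm receives less than 50 µg/day, a dose shortfall could be read as an effect of form, or a real advantage of SeMC could be hidden.

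Plasma selenium, one of the compliance checks in section 6.53, cannot settle this alone. It is also an outcome, and section 2.0 says that SeMet is incorporated non-specifically into proteins, so the plasma level may reflect form as well as dose.

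**Working it through.** **Inputs**
- Selenium per enriched onion: 60 to 80 µg, midpoint 70 (section 6.51).
- Meals per week: 3 to 5 (section 6.2).
- Onions per meal: not stated. The crop sum is 2 arms × 5 × 12 × 24 = 2,880, against about 3,000 onions grown, which implies about one per meal. This is taken as an assumption.

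**Formula.** Daily selenium = meals per week × onions per meal × µg per onion / 7.

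**The plan's own figure.** Five meals with a mid-range onion give 5 × 70 / 7 = 50.0 µg/day, so the stated amount reproduces at the maximum frequency.

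**Across the stated range, one onion per meal (µg/day)**

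| Meals/week | 60 µg/onion | 70 µg/onion | 80 µg/onion | Range as % of 50 |
|---|---|---|---|---|
| 3 | 25.7 | 30.0 | 34.3 | 51 to 69 |
| 4 | 34.3 | 40.0 | 45.7 | 69 to 91 |
| 5 | 42.9 | 50.0 | 57.1 | 86 to 114 |

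Only five meals bracket 50. The shortfall is 31 to 49% at three meals and 9 to 31% at four.

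**Without the one-onion assumption.** A meal of any fixed content delivers 5/3 = 1.67 times as much at five meals as at three. A meal that gives 50 µg/day at five meals gives 50 × 3/5 = 30 at three. One that gives 50 at three gives 50 × 5/3 = 83 at five.

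**Content needed to hold 50 µg/day.** The weekly total is 50 × 7 = 350 µg. Spread over five meals, that is 70 µg per meal. Over three meals it is 116.7 µg per meal, or 116.7/80 = 1.46 to 116.7/60 = 1.94 onions.

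**Un-enriched arm.** At 0.9 µg per onion, 0.9 × 3/7 = 0.39 to 0.9 × 5/7 = 0.64 µg/day. This agrees with the stated amount of less than 1 µg/day.

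**Effect on the planned statistics.** Section 7.0 assumes effects proportional to dose and a 1 SD range between groups. With 1 SD at 200 µg/day, the expected onion effect is 50/200 = 0.25 SD. At three meals it is 25.7/200 = 0.13 to 34.3/200 = 0.17 SD. With group means in SD units of 0, 0.25, 0.5, 1, (onion dose)/200 and 0, and a 5% level (assumed), the power of the six-group ANOVA is:

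| Onion dose (µg/day) | 18 per group | 24 per group |
|---|---|---|
| 25.7 | 0.793 | 0.912 |
| 50 | 0.772 | 0.897 |
| 57.1 | 0.769 | 0.895 |

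The overall test hardly depends on the onion dose.

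**The case against.** **One onion per meal is inferred.** This is correct. The supply sum can also be read as a weekly quantity of five onions, which gives 43 to 57 µg/day however many meals carry it. On that reading, 50 µg/day at 3 to 5 meals is coherent. The crop size does not exclude it: 350 µg/week needs 350/80 = 4.4 to 350/60 = 5.8 onions per volunteer. But no section says that meals are made up to a weekly total. Section 6.51 describes dishes from a common menu that are frozen and labelled only by colour. The document should say which reading is meant.

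**50 µg/day is attainable.** This stands too. A reader might infer that the arm is under-dosed or is not dose-matched. The documents do not support that, because five meals with a mid-range onion give exactly 50.

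**No dose-matched test is named.** Objective 1 mentions neither the 50 µg tablet nor matching. Section 7.0 plans a six-group ANOVA, a repeated-measures analysis and a separate analysis of the two onion groups. The contrast of onions with the 50 µg tablet is a fair inference from the equivalence, not a stated analysis.

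**The analysis does not use 50 as a dose.** A reader might take section 7.0 to code the onion arm as 50 µg/day. It does so only in the power calculation. The ANOVA treats group as a six-level factor, and section 7.0 itself puts the word equivalent in quotation marks when discussing the onion groups.

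**A shortfall would be visible.** Meals are assayed (section 6.61ii), consumption is recorded (section 6.2, Annex 16), and urine and plasma selenium are checked (section 6.53). The data will therefore exist, but the protocol does not say that they will be used to establish the delivered amount.

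**Conclusion.** The concern holds in a limited form. A single daily amount cannot be true across 3 to 5 meals of fixed content, and sections 4.1 and 7.0 carry that amount forward without qualification. Under the one-onion assumption, the onion arm could receive from about 26 to 57 µg/day. If content per meal is instead adjusted to frequency, the range narrows to 43 to 57, but the document does not say so.

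The consequence is possible confounding of selenium form with dose in any comparison of onions with Se-yeast. It is not a loss of power in the main ANOVA, nor proof that the arms will differ in dose. The 0.13 to 0.17 SD figures further depend on the plan's proportionality assumption and on 1 SD being reached at 200 µg/day.

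**What to change.** 1. Reconcile sections 4.1 (with Figure 1), 6.2, 6.51 and 7.0 so that meals per week, selenium per meal and the stated daily amount agree, and state the onion content of a meal. The values are for the sponsor to choose.
2. State that the selenium delivered in the onion arms will be calculated from the assayed selenium per meal (section 6.61ii) and the recorded meals (Annex 16). Report it by arm beside any comparison of onions with Se-yeast, so that the 50 µg/day equivalence is not taken as given.
3. Keep the ANOVA by randomised group as the main analysis. Delivered selenium depends on consumption after randomisation, so it serves to describe and interpret the comparison and does not replace the groups.

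The cost is protocol wording and one derived variable. The assays and records are already planned, and the sample size does not change.

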## 6.3 Sample Collection

### 6.31 Blood Samples

A total of six blood samples (including one taken at screening) will be taken throughout the course of the study, a total of 375mL of blood. On the day of the clinical screening, 15mL of whole blood will be taken. A volume of 8mL will be sent to BUPA for Full blood count and glucose. The other 7mL (in selenium free tubes) will be used to separate serum/plasma for the determination of the volunteer’s selenium levels. The serum/plasma samples will be labelled and stored at -80oC until analysis.

On the study days, 80mL of blood will be taken. A volume of 3mL will be sent to BUPA for a Full blood count. 10mL of whole blood will be used for the determination of serum/plasma selenium and alpha-tocopherol levels; 15mL of whole blood fractionated by centrifugation to produce platelets, serum/plasma and erythrocytes to look at the activities of selenoproteins and protein expression levels. A further 12mL will be used for RNA extractions and functional biomarkers of selenium status. 40mL will be required for use cellular and humoral immune response analysis (this will NOT be taken in only week 6).

### 6.33 Urine Samples

The procedure for collection of the sample will be explained to the volunteers. Researchers at the Institute of Food research have many years of experience in collecting urine samples from volunteers and are able to instruct volunteers to collect in a safe and hygienic manner. The urine samples will be brought in by the volunteers themselves when they arrive for their 2nd fasted blood sample in week 6.

### 6.34 Saliva samples

Saliva samples will be expectorated into clean plastic containers after blood samples have been taken in weeks 0 and week12. The volunteers will be advised not to brush or floss their teeth on the morning they are due to come in to give blood. The volunteers will then be asked to rinse their mouths out, at least twice, with cool water. In order to stimulate the production of saliva, the volunteer may be asked to chew sugar free gum for 1-2 minutes. After the time has elapsed, the volunteer will be asked to expectorate into an already labelled sterile wide necked tube (Universal), trying to avoid touching the mouth of the tubes with their hands. The saliva samples will be stored at -80oC until required.

## 6.4 Volunteer Randomisation

Ideally the study would be completely randomised, but this would compromise our ability to complete recruitment in the time allowed i.e. only accepting volunteers onto the study that like onions so that they could be randomised into any one of six groups (years 2 and 3 only as year one is the supplement study only). It would also beunethical to accept volunteers who had a dislike or intolerance to onions onto the onion part of the study.  Volunteers will as far as possible be randomly allocated to one of four groups in year one (0µg/day (placebo), 50µg/day, 100µg/day and 200µg/day of Se-yeast) and one of six groups in years 2 and 3 (the selenium supplements above as well as selenium-enriched and un-enriched onion groups).  There is no evidence to suggest that volunteers who do not or cannot eat onions will display any differences in immune function response or selenium status to those volunteers that do, and thus there will be no consequences of the study not being fully randomised.  However, as this is a new area of research, the preferences of all subjects recruited in the first year of the study will be monitored, and the possibility of differences by onion “preferences” investigated. Volunteers will be stratified by sex. The volunteer information document (annex 4) will clearly state that volunteers recruited in 2005 will be assigned to the supplement study only.

|  | Volunteers to be recruited | | |
| --- | --- | --- | --- |
|  | Selenium-enriched onions | Un-enriched onions | Selenium-Supplementation |
| Year 1 (2005-2006) | n=0 | n=0 | n=32 |
| Year 2 (2006-2007) | n=12 | n=12 | n=32 |
| Year 3 (2007-2008) | n=12 | n=12 | n=32 |

Table 1: Study groups outlined

## 6.5 Supply of Food and Supplements to Volunteers

**6.51 Selenium-enriched onions**

The selenium-enriched and un-enriched onions will be grown by the Division of Plant Science, University of Nottingham, under the supervision of [name], who is an authority on mineral nutrition of crops and is currently supervising a BBSRC CASE studentship programme on selenium enhancement with Hydro-Agri UK. The UK’s most popular variety of main crop onion (*Allium cepa* L., cv. Renate; a Rijnsburger type) will be grown by an experienced team of specialist horticultural scientists using standard commercial UK horticultural practices, and with the expertise in selenium fertilisation gained from the BBSRC CASE studentship. The onion crops will be harvested in August 2005 and 2006, and stored to ensure quality material is delivered for the intervention study. The selenium content of onions is approximately 1μg/100g (i.e. 0.9μg/onion) whereas Se-enriched onions contain 70-90μg/100g (i.e. 60-80μg/onion). Sufficient onions (~3,000) will be grown to provide enough onions for up to five meals per week for each volunteer for the 12 week intervention (Se-enriched: up to 5(meals) x12(weeks) x24(subjects); un-enriched: 5(onions) x12(weeks) x24(subjects)).

We will request that the different onions are labelled with different coloured tags (for example, or put in different coloured sacks). Meals will then be prepared with say, the red labelled onions, or the blue labelled onions without any one in the kitchen or the leading scientist knowing whether the red or blue labels related to enriched or un-enriched onions. As well as asking the manufactures to keep records of the coding i.e. red for selenium-enriched and blue for un-enriched say, we would ask that we too had an envelope with the information. This information would be held by a scientist not associated with the project, with the information being disclosed at the end of the study.

The volunteers taking part in the study will be given up to 5 meals with the same colour coding each week out of a minimum choice of 5 meals. All test meals will be prepared in a dedicated food preparation kitchen by the HNU diet cooks or in their absence by a member of the study team in possession of the Foundation Certificate in Food Hygiene, level 1. These dishes may include a beef carbonarde (beef in beer), three cheese pasta, ratatouille, shepherds pie and spaghetti bolognaise (sauce). The meals will be made with the enriched and the un-enriched onions and neither the scientist leading the study, nor the volunteer will know which type of onion they are consuming. Each set of meals i.e. the selenium-enriched and the un-enriched will be labelled by colour, for example all un-enriched meals labelled blue and all enriched meals labelled red.

The meals will be delivered to the homes of the volunteer once the volunteer’s capacity to store the food has been assessed, which will usually occur at the initial interview stage. For example if a volunteer has a large freezer compartment, then up to one month worth of food may be delivered in one go. If however the volunteer only has a small freezer box, then it may be more appropriate to deliver food on a weekly basis. All deliveries of food will be made either by refrigerated van or by a member of the study team; alternatively volunteers will be offered the option to pick up the meals themselves from the Human Nutrition Unit at their own convenience. No extra meals will be provided for members of the family and spouses of the volunteers as the cost are prohibitive. The volunteers will be reminded that possible side effects to eating any onions are bloating and wind.

